## Abstract

**Background:**

It is expected that increased demands on services will result from expanding numbers of older people with long-term conditions and social care needs. There is significant interest in the potential for technology to reduce utilisation of health services in these patient populations, including telecare (the remote, automatic and passive monitoring of changes in an individual's condition or lifestyle) and telehealth (the remote exchange of data between a patient and health care professional). The potential of telehealth and telecare technology to improve care and reduce costs is limited by a lack of rigorous evidence of actual impact.

**Methods/Design:**

We are conducting a large scale, multi-site study of the implementation, impact and acceptability of these new technologies. A major part of the evaluation is a cluster-randomised controlled trial of telehealth and telecare versus usual care in patients with long-term conditions or social care needs. The trial involves a number of outcomes, including health care utilisation and quality of life. We describe the broad evaluation and the methods of the cluster randomised trial

**Discussion:**

If telehealth and telecare technology proves effective, it will provide additional options for health services worldwide to deliver care for populations with high levels of need.

**Trial Registration:**

Current Controlled Trials ISRCTN43002091

## Background

It is expected that increased demands on health and social care services will result from the rise in the numbers of older people with long-term conditions and social care needs [1]. While there are alternative proposals about the implications of increasing numbers of older people on demand for services [2], much planning is predicated on expected increases in social and health service use amongst older people. Shifting the balance of care towards the home environment is seen as requiring an investment in 'upstream' interventions by providing enhanced primary and community care-based alternatives to secondary care and focusing on self-care at the patient level.

### The role of technology

In the current context of economic pressures and a desire to secure efficiency savings, there is significant interest in the potential for technology to reduce utilisation of health services in older people with long-term conditions and social care needs, while improving the quality and cost-effectiveness of care. There are a number of relevant types of telemonitoring technology and a lack of consensus concerning terminology. For the present paper we make the following distinction:

• Telecare is the remote, automatic and passive monitoring of changes in an individual's condition or lifestyle (including emergencies) in order to manage the risks of independent living. Examples include movement sensors, falls sensors, and bed/chair occupancy sensors. These technologies are generally provided to patients with social care needs.

• Telehealth is the remote exchange of data between a patient and health care professional to assist in the diagnosis and management of a health care condition. Examples include blood pressure and blood glucose monitoring. These technologies are generally provided to patients with long-term health conditions such as diabetes.

In the United Kingdom, the announcement of the Whole System Demonstrator pilots led to the subsequent award of funding to teams in three areas of England (Kent, Newham and Cornwall) to implement service redesign to support individuals with long-term and complex health and social care needs. This 'whole systems redesign' was designed to create multidisciplinary teams in health and social services and the development of integrated care plans to deliver care more effectively to these patient populations. An important part of the 'whole systems redesign' was the introduction of telemonitoring technology in the home to support the provision of these new services and serve as an 'effect multiplier' for changes in service delivery (See Figure 1). The aim of the Whole System Demonstrator trial is to evaluate whether telehealth for people with long-term conditions and telecare for people with social care needs can provide cost-effective care to improve outcomes, maintain independence, achieve significant gains in quality of life and reduce unnecessary acute hospital use and costs.

**Figure 1 F1:**
[figure not shown]
**Telecare and telehealth as an 'effect modifier' of wider system redesign**.

### Evidence for the effectiveness and cost-effectiveness of telecare and telehealth

Several reviews of the effectiveness of telecare and telehealth have been published both within specific disease areas [3-5] and across different areas [6,7]. Much of the available literature refers to pilot projects and the assessment of the impact of these devices on short-term outcomes and the majority of studies do not meet robust evaluation standards. Very few of the studies reviewed have assessed the longer-term or routine use of such technologies. A systematic review of 24 trials of interactive health communication applications [8] most closely relate to what is defined here as telehealth. In the review, telehealth had a significant positive effect on knowledge, social support, behavioural outcomes (e.g. calorific intake, exercise and medication taking) and clinical outcomes (e.g. asthma symptoms, HbA1c levels and body mass index). It was not possible to determine whether they had an effect on emotional outcomes or overall healthcare resource use. Another recent systematic review of telecare and telehealth interventions reported an emerging evidence base for the clinical effectiveness of telehealth technologies aimed at vital signs monitoring but insufficient high quality evidence for the effectiveness of telecare applications such as safety and security monitoring [9].

The clear potential of telehealth and telecare technology to improve care and reduce costs combined with the lack of rigorous evidence of actual impact means that a randomised controlled trial is required. The remainder of this paper will describe the protocol for the evaluation of the Whole System Demonstrator pilots and the methodological issues raised in the evaluation.

## Methods/Design

The broad research aim is to assess the effectiveness and cost-effectiveness of (a) telehealth in the management of patients with long-term health conditions, and (b) telecare in the management of patients with social care needs. The proposed trial is a large scale, pragmatic health technology assessment trial, designed to randomise suitably large numbers of patients and assess the impact of a broad class of telemonitoring technologies in the context of routine delivery of NHS care [10,11].

As with any pragmatic trial, the proposed design was a compromise between methodological, ethical and policy issues. The optimal assessment of the cost-effectiveness of a new health technology is a randomised controlled trial, and this was the initial basis for all design discussions. However, subsequent discussions with sites highlighted the importance of designing a trial that had the support of stakeholders, and that individual randomisation of patients was unlikely to be acceptable.

To deal with these issues, the proposed trial used a cluster randomised trial design (see Figure 2). Although many services provided to patients (especially those with social care needs) are delivered outside primary care, general practices were used as the unit of allocation because they are stable organisations involved in the care of all patients in each site.

**Figure 2 F2:**
[figure not shown]
**The basic trial design**.

General practices were randomised so that eligible patients within their populations would receive access to *one *technology (i.e. *either *telehealth or telecare). Each practice would thus provide intervention participants for one technology (e.g. telehealth) and control participants for the other technology (e.g. telecare) or vice versa. This ensured that equity of access existed at the level of the practice population, and that no practice was asked to risk randomisation to a no-treatment control where all patients would be denied access.^1^

Clearly, the introduction of a complex suite of telemonitoring technologies and the associated service changes raised more questions than could be answered with a conventional trial alone, so that the proposed cluster trial was used as a structure, around which a wider evaluative process was designed in line with current convention about the assessment of complex interventions [12,13]. The broad evaluation structure is outlined in Figure 3, and the research questions listed below.

**Figure 3 F3:**
[figure not shown]
**Research Themes**.

• *Theme 1: Service utilisation*. Does the introduction of telehealth or telecare result in reduction of service utilisation and costs of care?

• *Theme 2: Clinical effectiveness*. Does the introduction of telehealth or telecare result in improvements in quality of life, well being, self care, and carer burden?

• *Theme 3: Cost-effectiveness*. What are the economic consequences of introducing telehealth and telecare?

• *Theme 4: Patient and professional experience*. What is the experience of service users, carers and health and social care professionals during the introduction of telehealth and telecare?

• *Theme 5: Service delivery and organisation*. What organisational factors facilitate or impede the sustainable adoption and integration of telehealth and telecare?

The rest of this report will detail the protocol for the quantitative analysis of the core trial (Themes 1-3). A summary of the related qualitative work (Themes 4 and 5) can be found in Figure 4 and 5.

**Figure 4 F4:**
[figure not shown]
**Theme 4**.

**Figure 5 F5:**
[figure not shown]
**Theme 5**.

Themes 1-3 were all based on the same core trial design and involved the same population criteria and interventions, but the samples and outcome assessments differed. The core measure of service utilisation in Theme 1 was use of hospital services, to support a business care for the adoption of telemonitoring technologies in the United Kingdom. Due to the large skew in distribution of hospital use, a large sample of patients were required (see sample size calculation below). Therefore, all patients who receive telecare or telehealth in the practices involved in the evaluation were to have routine data on health and social care service extracted from existing data sources. This did not require the individual patient assessments required for Themes 2 and 3. Themes 2 and 3 used a subsample of patients who were assessed using patient reported outcome measures (PROMs) and health utilisation measures to provide a more comprehensive assessment of clinical and cost-effectiveness. The design is shown in more detail in Figure 6.

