#### (b) Waiting list controls

Telehealth and telecare participants randomised to the control arm received standard health and social care for 12-months and then, subject to re-assessment, were offered telehealth or telecare at the end of trial.

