### Trial procedures

General practices were approached by letter inviting them to take part in the trial. Once a practice had consented, potential participants for telehealth were identified in each site using existing registers of patients with long-term conditions in general practice. Potential participants for telecare in each practice were identified from databases held by social services departments.

To meet ethical obligations, patients were asked to complete and return a 'data sharing letter' if they consented to their data being shared with the research team. Once this letter was received, patients received a 'light touch' visit from a member of the project team in each site, where consent was taken to (a) participate in the main trial (Theme 1) and (b) the questionnaire study (Themes 2 and 3).

Participants who agreed to take part in the Themes 2 and 3 were subsequently contacted by a market research company to arrange a convenient time for the baseline interview. At this interview, patients received information about this part of the study and signed consent. The baseline assessment varied by participant status (i.e. COPD, heart failure, diabetes, telecare, carers) but each comprised a core of standardised PROMs. The PROMs were self-completed by the participant with the researcher on hand to explain or clarify. Data on health care utilisation were collected via interview. The average total time for assisted baseline interview completion was 80 minutes.

Carers of service users in the trial were identified by sites usually at the 'light touch' visit, either by the carer expressing an interest or via *snowball sampling *(i.e. asking participants if they had an informal carer at the baseline interview).

Each practice was allocated to groups via a centrally administered minimisation algorithm. The allocation determined the technologies available to each practice (i.e. either telehealth or telecare) and their associated patients. Following installation of the technologies, participants will be followed-up for 12-months. After 12-months, the 'usual care' groups were eligible to receive the appropriate interventions.

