### Analysis

The overall trial essentially involves two nested trials (one comparing telehealth with usual care, and one comparing telecare with usual care) which will be analysed separately but using identical procedures.

Unlike other evaluations of technologies in the NHS [40], the trial is not primarily designed to assess the effectiveness of any particular type of telecare or telehealth technology, and the primary analysis is at the level of the technology type (i.e. telehealth or telecare). There are no plans to conduct analyses of individual technologies.

#### (a) Themes 1 and 3

Baseline characteristics (e.g. age; sex; ethnicity; co-morbidities; risk of hospitalisation; typical hospital use) of the patients in the intervention and usual care arms will be compared and adjusted for where appropriate. Utilisation (inpatient admissions, bed day use, and cost) will be compared between the two groups for the three years before each patient receives the intervention, and the 12 months afterwards using appropriate statistical models for cluster randomised trials.

One method of analysing the results of Theme 1 will be using a risk stratification tool, to identify individuals at different levels of risk of future hospitalisation. Two such tools will be used, the Patients At Risk of Rehospitalisation (PARR) model and the Combined Predictive Model.^2 ^Both of these models are in use in the NHS to case-find patients for admission-avoidance programmes. The aim will be to understand which patients saw greatest changes in service use from the addition of telehealth or telecare, according to standard metrics used routinely to target services in parts of the NHS.

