### Advantages and disadvantages of the proposed design

Adoption of the cluster design means that individual patients are not randomised to technology or usual care. This overcomes concerns raised by the participating sites, who felt that individual randomisation was unlikely to be acceptable to patients or professionals: in the adopted design, all general practices will have immediate access to the roll-out of telemonitoring equipment for at least some of their patients. The design thus overcomes concerns about resentful demoralisation among practices [42] if some practices had been randomised to usual care for all their patients, especially as all participants are assessed for the technology after 12 months. The current study is a cluster randomised design, using general practices as the unit of randomisation. However, the present design is an 'individual cluster' design [43]. This means that a cluster randomised design has been adopted for various reasons, but the intervention is still delivered to individual patients. This is unlike a 'cluster cluster' design, where patients in the cluster cannot refuse the intervention (e.g. a water fluoridation trial).

Clearly, the planned analysis by type of technology (telehealth and telecare) ignores differences within technologies. The study has not been powered to explore the effects of individual technologies, but combining different technologies into the primary analysis will lead to debates about their comparability [44]. The qualitative data from Theme 4 may be a useful source of data on variation among users and professionals in their experience of different technologies.

It is important to note that all practices taking part in the evaluation are part of the Whole System Demonstrator pilots, and thus all practices and patients are potentially benefiting from the wider service redesign that is ongoing in these sites. Therefore, the study is assessing the added value of telehealth and telecare technologies over and above the effects of this wider service redesign, and not the benefits of whole systems redesign versus conventional care (see Figure 1). There will therefore be issues concerning the generalisability of the results, because the sites which are part of the Whole System Demonstrator pilots have been specifically chosen for their innovations in these areas of care.

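### The article conflicts with itself on who enters the Theme 1 comparison and from what date: receipt of equipment in some places, consent and practice allocation in others

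*Protocol article*

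**What the plan says.** Three places in the article tie Theme 1 to receipt of equipment.

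- Methods/Design, in the paragraph that separates the samples for Themes 1 to 3: "all patients who receive telecare or telehealth in the practices involved in the evaluation were to have routine data" on service use extracted.
- Trial procedures, last paragraph: "Following installation of the technologies, participants will be followed-up for 12-months".
- Analysis, Themes 1 and 3: utilisation is compared between the two groups "for the three years before each patient receives the intervention, and the 12 months afterwards".

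Other places define entry and arm differently.

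- Trial procedures, on the light-touch visit: "consent was taken to (a) participate in the main trial (Theme 1) and (b) the questionnaire study (Themes 2 and 3".
- Trial procedures, on allocation: "Each practice was allocated to groups via a centrally administered minimisation algorithm". The result decides which technology a practice's patients can have.
- Analysis, Themes 1 and 3: the baseline characteristics "of the patients in the intervention and usual care arms will be compared and adjusted for where appropriate".
- Waiting list controls: these participants "received standard health and social care for 12-months and then, subject to re-assessment, were offered telehealth or telecare" when the trial ended.

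The Discussion adds that "a cluster randomised design has been adopted for various reasons, but the intervention is still delivered to individual patients", and contrasts this with designs in which patients are unable to refuse.

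**The concern.** Practice allocation is what protects the comparison. Receipt comes later, depends on the individual patient and can be refused. A control patient faces no matching step during the 12 months, because nothing is installed.

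If the data set, the start of follow-up and the analysis window all hang on receipt, two things can go wrong in the Theme 1 primary outcome, the proportion admitted to hospital. First, consenting patients in intervention practices who never get equipment can drop out of that arm while similar patients stay among the controls. Second, the three years before and 12 months after have no defined centre for a control, so whoever builds the data set must invent a date. Either choice can shift the estimate, and the article does not settle either one.

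**Working it through.** **1. The passages side by side**

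| Question | Receipt wording | Consent and allocation wording |
|---|---|---|
| Who has Theme 1 data? | Those who receive a technology (Methods/Design) | Those who consent to Theme 1 (Trial procedures) |
| What sets the arm? | Not stated | Practice allocation (Trial procedures) |
| When does the 12 months start? | Installation or receipt (Trial procedures; Analysis) | Not stated |
| Does it work for controls? | No: no technology in the trial year | Yes for membership; no date given |

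Neither column gives a complete two-arm rule, and they disagree on the first row.

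**2. The plan's own sample size**

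Inputs from the Sample size calculation section: baseline 25%, relative risk reduction (RRR) 17.5%, so 0.25 × (1 − 0.175) = 20.625%; power 80%; two-sided 0.05; ICC 0.001. Assumed: 1:1 arms and cluster size m, which is not stated.

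n per arm = [1.96 √(2 p̄(1 − p̄)) + 0.8416 √(p₁(1 − p₁) + p₂(1 − p₂))]² / (p₁ − p₂)², with p̄ = 0.228125. This gives 1,443 per arm, or 2,886 in total. Multiplying by 1 + (m − 1) × 0.001 gives 2,912, 2,941, 2,970 and 3,004 for m = 10, 20, 30 and 42. The stated 3,000 reproduces and is not in dispute.

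**3. What dropping non-receivers from one arm could do**

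Assumptions: no true effect; 25% admission among all allocated patients in each arm; 1,500 allocated per arm; clustering ignored; a share q of the intervention arm never receives equipment and has k times the receivers' risk. The documents give neither q nor k.

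Receivers' risk = 0.25 / [(1 − q) + qk]. Spurious RRR = 1 − 1 / [(1 − q) + qk]. The rejection probability comes from a two-sided two-proportion normal test of 1,500 controls against 1,500(1 − q) receivers.

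| q | k | Receivers' risk | Spurious RRR | Rejection |
|---|---|---|---|---|
| 10% | 0.8 | 25.5% | −2.0% | 6% |
| 10% | 1.0 | 25.0% | 0 | 5% |
| 10% | 1.25 | 24.4% | 2.4% | 7% |
| 10% | 1.5 | 23.8% | 4.8% | 11% |
| 10% | 2.0 | 22.7% | 9.1% | 30% |
| 20% | 0.8 | 26.0% | −4.2% | 10% |
| 20% | 1.0 | 25.0% | 0 | 5% |
| 20% | 1.25 | 23.8% | 4.8% | 11% |
| 20% | 1.5 | 22.7% | 9.1% | 28% |
| 20% | 2.0 | 20.8% | 16.7% | 72% |

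Example, last row: 0.25 / (0.80 + 0.20 × 2.0) = 0.25 / 1.20 = 0.208, and 1 − 1/1.20 = 16.7%.

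**4. What keeping everyone costs**

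Assume receivers gain the full 17.5% and non-receivers gain nothing and have the same untreated risk. The all-allocated RRR is then 17.5% × (1 − q). With m = 20 (design effect 1.019):

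| q | All-allocated RRR | Power at 3,000 | Total for 80% power |
|---|---|---|---|
| 5% | 16.6% | 77% | about 3,270 |
| 10% | 15.8% | 72% | about 3,660 |
| 20% | 14.0% | 61% | about 4,660 |

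**The case against.** The strongest reply is that the Methods/Design sentence was never meant to define an analysis set. Taken literally it leaves out every control as well, which cannot be intended when the Analysis section compares intervention with usual care. Its evident purpose is to contrast the full routine-data sample with the smaller assessed sample of Themes 2 and 3.

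That part of the reply stands, and it rules out a stronger reading. A reader might infer that Theme 1 is defined by receipt instead of consent, that the plan removes non-receivers from the intervention arm only, and that the result is a false benefit. The article does not support this. Trial procedures makes consent the entry to Theme 1, no section states a one-sided exclusion, and the direction of any bias depends on risks that are not reported. Controls are offered equipment after re-assessment, which suggests an earlier assessment, so some screening for suitability may have applied to both arms. The detailed design figure and the participant flow diagram are not in the text available, and the analysis plan may say how non-receivers are handled. The lack of an intention-to-treat statement in the article is therefore no finding.

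What does not stand is that this is one loose sentence. Installation or receipt recurs as the time anchor in Trial procedures and in Analysis, where it is applied to both groups although controls receive nothing in that year. The wording has to be repaired by whoever builds the data set, and one obvious repair, receivers against all consenting controls, is the one open to bias.

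**Conclusion.** The point holds as an internal contradiction over the population and time origin for the Theme 1 primary outcome. It is not a demonstrated exclusion of patients. It needs to be reconciled before the Theme 1 data set is built.

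Its possible size is wide. Under the stated assumptions, adverse cases run from a small distortion (RRR 2.4%, about 7% rejection) to one close to the 17.5% the trial was sized to detect (16.7%, about 72% rejection). The upper end needs both 20% non-receipt and double the risk. The rejection figures ignore clustering. The missing index date for controls needs no assumption: it follows directly from the text.

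**What to change.** Reconcile Methods/Design, Trial procedures and Analysis with one statement, for example: routine data will be extracted for all patients in both arms who consented to Theme 1; they will be analysed in the arm to which their practice was allocated, whether or not equipment was installed; and the periods before and after will be counted from an index date defined the same way in both arms, such as the date of consent or of the light-touch visit. Any as-received comparison should be labelled secondary, and the number of allocated non-receivers reported.

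The practical cost is wording, plus extraction of routine data for patients who have already consented. The statistical cost is dilution, which is more than slight if non-receipt is common, as the last table shows; it should be acknowledged beside the stated 80% power. If the 17.5% was already meant as an average over all allocated patients, that loss does not arise. An index date at consent also places any wait for installation inside the intervention arm's 12 months, which dilutes the effect further but treats both arms alike.
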